##### Stroop task test

We will use the New Stroop Test II (Spanish version). This test measures selective attention, cognitive flexibility, and processing speed. It is used to evaluate executive function [54]. The test consists of two control tasks: a Stroop task and a reverse Stroop task. The number of correct answers, reverse-Stroop interference rate, and Stroop interference rate will be calculated.

##### Physical activity enjoyment scale

Before, during, and immediately upon completion of each protocol, participants will also rate their perceived enjoyment according to the physical activity enjoyment scale, which has been validated by Kendzierski and DeCarlo [55]. Each item is rated on a seven-point bipolar scale with four representing a neutral point in terms of how much the respondent enjoyed the exercise.

##### Physical activity and sedentary behavior

The Actigraph GT3x dual-axis accelerometer (Actigraph, Pensacola, FL, USA) and ActivPAL monitor (PAL Technologies Ltd., Glasgow, UK) will be used. The Actigraph GT3x measures vertical accelerations from 0.05*g* to 2*g*, sampled at 30 Hz, at 5-s epoch intervals. The ActivPAL summarizes data in 15-s epoch intervals over 24 h at a sampling frequency of 10 Hz. Before the beginning of each MOVI-2 program session, the accelerometer will be positioned at the waist in line with the right axilla, at the level of the iliac crest of the right hip and secured by an elastic belt round the hip. The Actigraph GT3x has been validated for estimating energy expenditure during physical activity in a youth population [56]. Data from the accelerometer will be used to calculate the average counts/min for each game. Accelerometers will also be worn continuously for seven consecutive days to record physical activity intensity levels and patterns, as well as sleeping habits. Participants will also complete a diary log. Data stored in the device will be analyzed using the ACTi-life 6.01 software.

##### Dietary assessment

To determine the average habitual energy and macronutrient intake, a detailed 24-h diet record will be obtained from each adolescent for one weekday and one weekend day during the 1-week baseline period. Food intake analysis software (FAO/INFOODS, Report of the Technical Workshop on Standards for Food Composition Data Interchange, Rome 2004) and national food composition tables (for specific foods) will be used to analyze the total energy and macronutrient intake of each subject’s 24-h diet. The dietary assessment will be conducted by a registered nutritionist.

##### Sociodemographic information

Baseline sociodemographic values (sex, highest educational level attained by mother/father, composition of household, others), which could act as covariates or confounders for the tested treatment modality, will also be collected. The surveys will include questions on age, education, occupation, income, health history, and alcohol consumption, among others.

##### Side effects and monitoring

The study will be conducted according to good clinical practice and standard operating procedures. It will be monitored by the Human Rights Committee at the Universidad del Rosario Coordinating Centre, a committee composed of experts in physical exercise and sports medicine, plus physical therapists, physical educators, and clinical epidemiologists. Interim monitoring reports will be submitted to the experts, focusing on patient intake, adherence to the protocol, baseline comparability of treatment groups, completeness of data retrieval, and adverse events. All adverse events will also be reported to the Universidad del Rosario Ethics Committee. To standardize the study procedures, an operations manual has been written, and comprehensive training sessions will be held prior to initiation of the trial. An independent researcher will be in charge of auditing all assessment staff to record all of these events for the participants over the study period.

### Power calculation and sample size

Change in liver fat is the primary outcome of this study. For liver fat measured by a FibroScan 502®, a sample size of 100 will have 80% power to detect a difference in hepatic fat of 5.0% assuming a standard deviation of 4.1% and an α of 0.025 for a two-sided significance level. Assuming a maximum a loss of follow-up of 10%, we decided to recruit a total of 100 subjects, 25 participants for each group. We assume that the dropout rate will be similar to that in our previous studies performed in a young overweight population with a similar age range and a similar intervention program [18, 23–25, 57–59]. The sample size will allow for multivariate analyses with up to three predictors, assuming moderate size effects.

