### Statistical analysis

The final data will be analyzed using IBM SPSS 22.0 (SPSS, Inc., Chicago, IL, USA) and SAS software (SAS Institute Inc., Cary, NC, USA). An exploratory analysis will be performed to determine the frequency, range, variability, and distribution type for each variable to establish the most appropriate statistical test when comparisons are necessary. These analyses will assess the primary outcome (hepatic fat) and will be undertaken using the intention-to-treat principle. The intention-to-treat analysis for this study will include all participants, including those who are not fully compliant and those with missing outcome data.

Because this is an experimental design with the primary and secondary outcomes measured twice, the first at baseline (*t*_0_ = 0 months) and the second after the interventions (*t*_1_ = 6 months), for four study groups, a comparative analysis between the measurements will determine the differences. A linear mixed model with repeated observations will be used for these comparisons, when appropriate, for each dependent variable. Subsequently, a multivariate analysis will be carried out, and the autocorrelation between repeated measures will be taken into account. We will use longitudinal analysis methods, such as a generalized estimating equation approach, to control the differences among measurements at baseline and to incorporate incomplete observations into this analysis. Pearson correlations will be calculated between the maximal values of the primary and secondary outcomes. Finally, we will investigate whether there is an interaction between the two interventions for the primary outcome after 30–40 min of supervised HIPE and LIPE or combined training (HIPE + LIPE). For these analyses, we will include appropriate interaction terms in the models [60]. We plan to report regression coefficients for the interaction terms and their 95% confidence intervals.

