## Discussion

The relevance of this project is that the results obtained from the objectives proposed will contribute to our understanding of the links between excess weight and alterations in hepatic and adipose metabolism. Moreover, we may be able to identify biomarkers for metabolic abnormalities associated with central obesity that are involved in the induction of oxidative dysfunction processes via lipotoxicity, which is common in physical inactivity and obesity, such as pathologies related to the cardiometabolic system. The study of biomarker profiles in adolescents with metabolic syndrome and obesity compared to a normal weight population could assist in the early diagnosis of cardiovascular diseases. Future studies are warranted to verify the relevance of the biomarkers associated with obesity and elucidate the underlying biochemical processes.

Currently, the management of overweight conditions and public information on the topic have focused on treatments such as caloric restriction, physical exercise, and different drugs. There have been promising results, due to the distinct metabolic adaptations that can prove beneficial for individuals with excess weight. Thus, our research hypothesis is that some physical exercise programs will generate a higher reduction of fat in liver than other interventions. In addition, there may be improvements in the hepatic metabolism and cardiovascular health of overweight/obese adolescents from the district of Bogotá.

At a clinical level, interventions to prevent excess weight and sedentary habits are very costly and the results in the pediatric setting are discouraging and not very cost-effective [60–62]. Hence, our research seeks to evaluate the impact of the interventions, and whether they are easy to implement, safe, economic, and free of secondary effects. The research focuses on assessing hepatic metabolic activity (fat content, as a primary outcome) and bodily composition, blood pressure, insulin sensitivity, lipid and carbohydrate metabolism, and physical condition (secondary outcomes), which are highly relevant.

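### The stated 80% power does not follow from the stated inputs, and the same 100 participants serve both as the powered size and as the number recruited after a 10% loss

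*Protocol article*

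**What the plan says.** All the sample-size inputs stand in one paragraph of the protocol article, under Power calculation and sample size.

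- Endpoint: "Change in liver fat is the primary outcome of this study".
- Power claim: "a sample size of 100 will have 80% power to detect a difference in hepatic fat of 5.0% assuming a standard deviation of 4.1"%, with a two-sided alpha of 0.025.
- Loss to follow-up: at most 10%.
- Recruitment after that loss is considered: "we decided to recruit a total of 100 subjects, 25 participants for each group".

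The paragraph does not say which contrast the 5.0% refers to, whether 4.1% is the SD of the change or of one visit, or why alpha is 0.025. Allocation is equal across the four arms (second Blinding and randomization section). The Statistical analysis section plans comparisons among the four groups with a mixed model, and an interaction analysis for the primary outcome. The Primary outcome section gives the measurement in dB/m, whereas the sample-size inputs, like Table 2, are in %.

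**The concern.** A difference of 5.0 against an SD of 4.1 is a standardised effect of 1.22. That is large, and 25 per arm should detect it with far more than 80% power. The printed power and the printed inputs therefore cannot both be right.

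The paragraph also uses 100 twice: as the size that yields the power, and as the number recruited once 10% loss is allowed for. If 100 must be analysed, recruitment has to be higher. If 100 already includes the loss, the power statement belongs to about 90.

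This is the only sample-size justification in the article. How a null result is read depends on whether the trial had power in the mid-90s or around 70%.

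**Working it through.** **Inputs** (Power calculation and sample size): difference 5.0, SD 4.1, two-sided alpha 0.025, N = 100 as 4 × 25, loss 10%. After loss, 100 × 0.9 = 90, which is 22.5 per arm; I use 22.

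**1. The plan's figure as printed.** Two-arm comparison with d = 5.0/4.1 = 1.22.

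Normal approximation: power = Φ(Δ/(SD·√(2/n)) − z₀.₉₈₇₅), with z₀.₉₈₇₅ = 2.241.

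- n = 25: SE = 4.1 × √(2/25) = 1.160; 5.0/1.160 = 4.312; Φ(4.312 − 2.241) = 98.1%.
- n = 22: SE = 1.236; 5.0/1.236 = 4.045; Φ(4.045 − 2.241) = 96.4%.

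The noncentral t gives 97.5% and 95.4%. The stated 80% is not reproduced.

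**2. Number needed for 80%.** n = 2(2.241 + 0.842)² × (4.1/5.0)² = 12.8, so 13 per arm. The noncentral t gives 14.1, so 15 per arm or 60 in total. With 10% loss, 15/0.9 = 16.7, so 17 per arm or 68 in total.

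**3. Four-group F test at 0.025.** The least favourable pattern with a maximum difference of 5.0 has two extreme means and two in the middle (f = 0.43). Power is 92.4% at N = 100 and 88.7% at N = 90. This is not 80% either.

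**4. Loss to follow-up.** If 100 analysed participants were required, recruitment would be 100/0.9 = 111.1, or 112 (28 per arm) in equal arms. The plan recruits 100, so no allowance was added to the number said to give 80%.

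**5. Readings that come near 80%.** Each needs something that the paragraph does not state.

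*(a) 4.1 is a single-visit SD and the change is analysed.* SD of change = 4.1 × √(2(1 − r)), where r is the pre-post correlation, an assumption here. Noncentral t, alpha 0.025:

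| r | SD of change | 25 per arm | 22 per arm |
|---|---|---|---|
| 0 | 5.80 | 76.6% | 70.3% |
| 0.15 | 5.35 | 83.6% | 77.9% |
| 0.2 | 5.19 | 85.9% | 80.5% |
| 0.5 | 4.10 | 97.5% | 95.4% |

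*(b) A 2×2 interaction contrast of 5.0.* SE = 4.1 × √(4/25) = 1.64, and 5.0/1.64 = 3.05. Power is 79.0% by the normal approximation and 77.9% by t. With 22 per arm these are 73.2% and 71.8%.

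**6. Detectable difference at 80% power on the printed SD and alpha** (noncentral t).

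- 25 per arm: 0.896 × 4.1 = 3.7 points.
- 22 per arm: 0.958 × 4.1 = 3.9 points.

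**7. Alpha.** 0.025 = 0.05/2. Splitting 0.05 over three comparisons with control gives 0.0167, and over six pairwise comparisons 0.0083. On the printed inputs, 25 per arm still has 96.3% and 93.5% power at these levels (t). The sample size therefore does not hinge on the choice.

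**The case against.** The strongest reply is that the error is harmless. On the printed inputs the trial has more power than claimed, before and after the loss, so neither the number of participants nor the analysis has to change. This stands for those inputs, and it is why the point is not graded higher. It does not settle the matter, because it assumes that 4.1 is the SD of the quantity analysed, which the protocol does not say.

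A second reply is that 80% may be right under an intended reading. That is possible. With 4.1 as a single-visit SD and a correlation of about 0.2, 22 per arm gives 80.5%, so the 80% could even include the loss. The planned interaction analysis also comes near 80% at 25 per arm. A reader might infer that no reading reproduces the figure once the loss is counted; that goes too far. What holds is that each such reading needs a correlation or a contrast that the paragraph omits.

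A reader might also infer that alpha 0.025 is itself an error because it matches neither three nor six comparisons. The document does not support this. It states no overall 5% family-wise level and no Bonferroni split, and a multiplicity procedure may sit in an analysis plan that is not shown. The sentence "We plan to report regression coefficients for the interaction terms and their 95% confidence intervals" concerns interaction terms only and does not set the level for arm comparisons. The Discussion's hypothesis, "our research hypothesis is that some physical exercise programs will generate a higher reduction of fat in liver than other interventions", is not a success rule. What remains is narrower: the protocol fixes 0.025 and gives no basis for it in a four-arm design.

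**Conclusion.** Wrong as written. With difference 5.0, SD 4.1, two-sided alpha 0.025 and 25 per arm, pairwise power is 97.5%, not 80%; with 22 evaluable per arm it is 95.4%. The four-group F test has about 92% at N = 100 and 89% at N = 90. About 15 per arm would give 80%. The number 100 is used both before and after a 10% loss, so no allowance was made and about 90 will be evaluable.

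A reader might conclude that the trial is underpowered. The document does not show this: power after loss falls to about 70% only if 4.1 is a single-visit SD with zero pre-post correlation, which is not stated. Equally, 95% holds only if 4.1 is the SD of the analysed change and a pairwise contrast was meant. The defect is that the paragraph does not let the reader choose between them.

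This should be fixed. It is not critical, since on the printed inputs the error is conservative. The figures assume equal arms, a common SD, normal outcomes and loss spread evenly over the arms.

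**What to change.** Keep N = 100 and rewrite the sample-size paragraph so that it can be reproduced:

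1. Name the contrast that is powered (exercise versus control, any pair, the four-group test or the interaction).
2. Say whether 4.1 is the SD of the change or of a single visit; if the latter, give the assumed pre-post correlation.
3. Give the difference and SD on the scale of the primary measure, dB/m, or explain how the % values relate to it.
4. State the basis for a two-sided alpha of 0.025 in a four-arm trial.
5. Give power or detectable difference for both 25 randomised and 22 evaluable per arm. On the printed inputs this is 97.5% and 95.4% for 5.0 points, or 3.7 and 3.9 points at 80% power. These figures need recalculating if items 1 to 4 change the inputs.

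A named multiplicity procedure, such as Dunnett's test against control, is one option for item 4. It is a choice for the trial team and not part of the error.

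The cost is one reworded paragraph. On the printed inputs no extra participants are needed. If a single-visit SD with a low correlation was meant, the sponsor would have to state openly that power after loss may be nearer 70%.

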### Blinding and randomization

Each participant will have a 0.25 probability of being assigned to any study group. This assignment will be made through previously constructed balanced blocks. These blocks permit an equi-probabilistic assignment and ensure that each group has the same number of participants. This assignment mechanism will continue until all 100 participants have been assigned to their interventions. The study’s health personnel will act independently of the personnel in the school from where the participants are selected. Therefore, they do not carry out any school activities and their tasks are limited to collecting data for this study. The assignment codes will be maintained in a confidential file in the research center of the coordinating group and will be opened when the study analysis is finished. At the beginning and end of their participation in the study, the primary and secondary outcomes will be determined for each of the patients.

Given that physical exercise is an intervention that cannot be masked from the participants or researchers, professionals who are unaware of each subject’s group assignment will perform the measurement and analysis of the resulting variables. To ensure masking, randomization will be applied through balanced blocks and an alphabetical code will be assigned to each study group. This code will be in the custody of the administrative coordinator of the research group and will not be revealed to the professionals in charge of processing the data until the analysis with coded interventions has terminated.

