## Methods/design

### Study design, setting, and participants

The HEPAFIT study is a single-blind parallel-group randomized controlled trial (ClinicalTrials.gov ID NCT02753231). All parents or guardians will provide informed written consent and all the adolescents must give assent before being enrolled in the study. The study received ethical approval from the Medical Research Ethics Committee of the University of Rosario (ID UR-21042016). Random allocation to treatments will be performed at the individual level.

The study will include 100 adolescents (50% females) between 11 and 17 years of age attending to two public schools in the urban area of Bogotá D.C., Colombia. Inclusion criteria include primary overweight/obese status, defined according to the International Obesity Task Force [28], inactivity (no habitual participation in exercise more than once a week in the previous 6 months), and having at least one parent or caregiver willing to participate in the program sessions. Adolescents eligible for the present study will be invited to a pre-test, which will include a medical interview at the Centre for Studies of Physical Activity Measurements (in Spanish, CEMA), School of Medicine and Health Sciences, University of Rosario, Bogotá, Colombia. Risks will be minimized by identifying contraindications to the testing and training protocols via a health history and a thorough physical examination prior to the testing sessions. The exclusion criteria include having a clinical diagnosis of cardiovascular disease, having type 1 or type 2 diabetes mellitus, being pregnant, using alcohol or drugs, and not having lived in Bogotá for at least one school year. Adolescents with other causes of liver disease in the pediatric population that produce elevated liver enzyme levels will be excluded. These will be identified by screening for hepatotropic viruses (hepatitis A, B, and C, cytomegalovirus, and Epstein–Barr virus) and alpha-1 antitrypsin (A1AT) levels as well as autoantibodies and immunoglobulin G to rule out A1AT deficiency and autoimmune hepatitis, respectively. This study aims to investigate the effects of these interventions on risk factors for type 2 diabetes (i.e., its focus is prevention) rather than looking at their effects on treatment outcomes. Therefore, participants with established type 2 diabetes are excluded.

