### Blinding and randomization methods

The randomization into the four study arms will be performed by CEMA using a block randomization strategy with a block size of four. Since growing adolescents have an increasing body size and are undergoing developmental changes, a control group is necessary to detect changes due to training. After completing the baseline measurements, eligible participants will be randomly assigned to either the control or exercise training groups. The principal investigator will coordinate the allocation sequence, and randomization will be computer-generated. All participants and study personnel (including investigators, trainers, and statisticians) will be blinded to treatment allocation throughout the trial protocol. Access to the allocation code will be restricted to one study statistician who will not perform the final study analyses. Randomization will be conducted independently using sealed opaque envelopes. These procedures are also detailed in the study operations manual. Moreover, the importance of maintaining the blinding and allocation concealment will be reinforced by regularly scheduled conference calls at the sites and daily meetings with the field investigators (Fig. 1).

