The MOVI program uses attractive alternative materials not often used in the subjects’ daily lives or in the standard physical education classes. It is accessible, given that it occurs at the end of the classroom activities in the school’s facilities or nearby. It is free of charge and does not require the provision of any specific equipment. In its first edition, the MOVI program showed a moderate effect on reducing adiposity and improving the lipid profile but did not significantly improve global cardiometabolic risk or lower insulinemia [32]. In the second edition (MOVI-2), the duration and intensity of the sessions were increased and it was shown to enhance the development of muscle strength further. Likewise, analyses showed reduced adiposity in both sexes, and an improvement in the girls’ cardiovascular risk profile (low-density lipoprotein cholesterol or LDL-C and insulin) was observed [33]. The MOVI-2 program sessions that will be used in this work are the following:

Frequency: 3 days per week excluding holidays and vacation periods

Duration: 60 min, structured into 5 min of warm-up, 45 min dedicated to the main training curriculum, and 10 min dedicated to returning to a rest state

Protocol: Each of the sessions will work on activities based on health-related physical fitness (cardiovascular and muscle endurance and flexibility) at an intensity of between 8.0 and 11.7 metabolic equivalents (MET). All the games were performed previously by 32 schoolchildren during sessions of the MOVI-2 program while indirect calorimetry (through a portable gas analyzer), cardiac frequency, and accelerometry were evaluated for each game [34]. In addition, we have previously monitored the implementation of all the games with overweight/obese adolescents from Bogotá (unpublished observations).

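### The blocks of four are not described as stratified by school, and no school term is named in the analysis, although pupils come from and train in two schools: a chance-imbalance and precision point that is cheap to fix

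*Protocol article*

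**What the plan says.** The participants are 100 adolescents "attending to two public schools in the urban area of Bogotá D.C., Colombia" (Study design, setting, and participants). The same section fixes the unit of allocation: "Random allocation to treatments will be performed at the individual level".

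The allocation is described in two places. Blinding and randomization methods has it done "using a block randomization strategy with a block size of four". Blinding and randomization, later in the article, adds: "Each participant will have a 0.25 probability of being assigned to any study group", and "This assignment mechanism will continue until all 100 participants have been assigned to their interventions". On what the blocks achieve, it says: "These blocks permit an equi-probabilistic assignment and ensure that each group has the same number of participants". Neither section names school, or any other factor, as a stratum.

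School is also where the intervention is delivered. Of the exercise program, the section on the high-intensity class says that "it occurs at the end of the classroom activities in the" school's own premises or close by. The Statistical analysis section plans a linear mixed model and generalized estimating equations that allow for baseline differences. It mentions no school term.

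**The concern.** With two recruiting and training sites, school is the obvious factor on which to balance the arms. Equal arm totals do not ensure that each arm draws the same share from each school. If the 6-month change in liver fat differs between the schools, for whatever reason, an uneven split moves an arm difference by the product of two quantities: the difference in school share between the arms, and the difference in change between the schools. With 25 pupils per arm, a few pupils more or less make a visible difference in share. What is at stake is the precision of the arm comparisons and how convincing the one realised allocation looks.

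**Working it through.** **Inputs from the article.** Four arms, equal allocation, blocks of four, 100 pupils, two schools; SD 4.1 and target difference 5.0 percentage points of hepatic fat, α 0.025 two-sided (Power calculation and sample size).

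**Assumptions, because the article does not give them.** The split between schools (50:50, with 70:30 as a variant), the order of enrolment, and the size of the school difference in change (0.5 SD = 2.05 points; 1 SD = 4.1 points).

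**1. The plan's own figure.** 100 / 4 = 25 complete blocks, so exactly 25 per arm. The statement about equal group size is correct.

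**2. School split, mixed enrolment.** If pupils of the two schools arrive in random order, the number from one school in an arm is hypergeometric.
- Variance of one arm's count: 25 × 0.5 × 0.5 × 75/99 = 4.73, SD 2.18.
- Covariance between two arms: −25 × 25 × 0.25/99 = −1.58.
- Variance of the difference between two arms: 2 × (4.73 + 1.58) = 12.6, SD 3.55 pupils, or 3.55/25 = 14 percentage points.

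Simulation of the blocks of four (40,000 runs) gives the same SD:

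| Enrolment | Gap of 5 or more of 25, given pair | Same, largest gap among four arms | 95th percentile, given pair |
|---|---|---|---|
| Mixed, 50:50 | 21% | 58% | 28 points (7 pupils) |
| Mixed, 70:30 | 17% | 51% | 24 points (6 pupils) |
| One school after the other | 0% | 0% | 4 points (1 pupil) |
| Separate lists per school | 0% | 0% | 4 points (1 pupil) |

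The third row follows from the block size. Every complete block holds each arm once, so only the one block that straddles the change of school can be uneven, and by at most 1 pupil.

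**3. Shift of an arm difference in one realised trial.** Shift = gap in school share × school difference. At the mixed 50:50 95th percentile this is 0.28 × 2.05 = 0.57 points, or 0.28 × 4.1 = 1.15 points, against the target of 5.0. With separate lists and the larger school difference it is 0.04 × 4.1 = 0.16.

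**4. Precision.** With no school difference, the SD of an arm difference is √(2 × 4.1²/25) = √1.345 = 1.16. Mixed enrolment without a school term adds (0.142 × school difference)²:
- 0.5 SD: √(1.345 + (0.142 × 2.05)²) = √(1.345 + 0.085) = 1.20.
- 1 SD: √(1.345 + (0.142 × 4.1)²) = √(1.345 + 0.339) = 1.30.

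Simulations gave about 1.19 and 1.29 to 1.30. With a school term they gave 1.15 to 1.17 for either school difference. At 1 SD the variance without the term is about (1.30/1.17)² = 1.23 times that with it.

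**5. Type I error.** In 20,000 simulated two-arm comparisons at each school difference (0, 2.05 and 4.1 points), the rejection rate under no arm effect was 0.0246 to 0.0257, with or without a school term. The mean estimated arm difference was about 0.

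**The case against.** The best reply is that nothing in the article is wrong on this point. The statement about equal groups is arithmetically right. The article never says that there is a single list, and continuing until 100 are assigned is compatible with one list per school. It refers to an operations manual for the procedures, and a covariate list is what an article commonly leaves to the full protocol or analysis plan. This stands in part. The text does not prove that school is ignored, and the point has to be put as something not described. But the allocation is described in two sections, with equal group size as the only balance, and strata have to be set before randomisation, so an analysis plan could later supply only the covariate.

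A reader might infer that the arms are balanced only once all 100 are in. They are not: blocks of four rebalance after every fourth assignment, and sequential enrolment would give near balance by school. The protection would then come from the enrolment order, which the article does not state.

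A reader might also infer that school differences bias the comparison. Allocation is individual, so the imbalance is random; its mean effect is about zero and the type I error holds.

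Extreme splits are uncommon too. Under mixed 50:50 enrolment, two arms at 17:8 and 8:17 (a gap of 9 or more pupils) occur in about 1.7% of allocations for a given pair and 7.7% for any pair.

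Finally, the school difference in change may be small. Control for baseline largely removes stable differences in level, the standard class is prescribed nationally at 60 minutes a week, and the monitors are engaged and trained for the program. This is fair, and it is why the school difference is carried as an assumption.

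**Conclusion.** The point holds as a cheap improvement in design and analysis, not as an error that threatens validity. As described, the blocks are not stratified by school and no school adjustment is named, although the trial recruits and trains in two schools. Under randomly mixed enrolment, noticeable differences in school share between arms are common (5 or more of 25 in about 21% of allocations for a given pair at 50:50). Under school-by-school enrolment they are negligible.

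The effect is proportional to both the realised imbalance and the school difference. At an assumed 0.5 SD the gain from a school term is slight, and at 1 SD it is modest. The documents support neither a claim of systematic bias nor one of an inflated type I error. The conclusion rests on the assumed split, enrolment order and school difference, none of which the article gives.

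**What to change.** State whether the block lists are kept separately by school. If they are not:

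- Prespecify school as a fixed effect in the primary and all secondary models. This remains possible for pupils already randomised; the article gives recruitment as January to December 2018.
- Use a separate list of blocks of four for each school for pupils not yet randomised.

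The cost is a second list and one model degree of freedom. An incomplete last block in each school means that arm totals may be 24 to 26 instead of exactly 25. If replacing the list during recruitment is impractical, the school term alone recovers the precision, though not the balance in numbers.
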